**9.1 Quality control for researchers**

The recruitment process for the study was meticulously orchestrated to ensure the selection of appropriate subjects. Specialized recruiters conducted screenings with stringent adherence to the predetermined inclusion and exclusion criteria. Subjects who satisfied all inclusion criteria and none of the exclusion criteria were systematically enrolled and assigned a unique study number reflecting their sequential order of inclusion. Conversely, individuals who failed to meet the necessary criteria were excluded from the study. The recruiters maintained detailed records of each exclusion, documenting both the quantity and the specific reasons for disqualification.

**9.2 Quality control of study participant enrolment**

The recruitment protocol for the study was executed with precision by specialized recruiters who adhered strictly to the established inclusion and exclusion criteria. Candidates who fulfilled all the inclusion criteria while not meeting any of the exclusion criteria were systematically included in the study and sequentially assigned a study number. Conversely, individuals who did not meet the qualifying criteria were excluded. The recruiters meticulously documented each exclusion, noting the total number of exclusions along with the specific reasons for each disqualification.

**9.3 Quality control of the intervention process**

Throughout the duration of the intervention, certified coaches were mandated to demonstrate uniform and standardized movements, providing continuous instruction to participants and promptly rectifying any deviations in form. Concurrently, researchers meticulously oversaw each training session, documenting attendance on-site. They calculated the attendance rate post-intervention and instituted a protocol whereby participants unable to attend centralized sessions were required to request and log their absence in advance. This measure was implemented to guarantee adherence to the prescribed exercise regimen of one hour, thrice weekly. To mitigate the potential disruptions caused by inclement weather conditions such as rain or snow, indoor facilities like community centers were strategically selected as the venues for the intervention.

**9.4 Quality control of data management**

To uphold the integrity of the data collection process, researchers implemented standardized methodologies aimed at minimizing bias. This involved meticulous storage of original documents, which were then individually verified post-assessment to confirm data completeness and accuracy. Such diligence ensures that the collected information is both reliable and valid for subsequent analysis.

1. **Statistical analysis**

**10.1 Power calculation**

The prevalence of falls and fractures due to the diminution of muscular mass and function underscores the clinical urgency and grave repercussions associated with sarcopenia. Drawing upon empirical evidence from a preceding trial targeting older adults predisposed to falls ^[14]^, the Short Physical Performance Battery (SPPB) is employed as the primary efficacy index. Utilizing a two-sided test with a power of 90% and a significance level of 5%, the requisite sample size for a single intervention group is deduced to be approximately 36. Accounting for an anticipated dropout rate of 20%, each group necessitates 45 participants diagnosed with sarcopenia.

**10.2 Data analyses**

Following an intention-to-treat (ITT) protocol, those whose cumulative time of exercise reaches 80% of the amount to be completed and not higher than 120% of that will be classified into per protocol set (PPS). Categorical variables will be presented as percentages or frequencies. As for continuous variables, normally distributed data will be described by mean ± standard deviation, while non-normally distributed data will be described using median [interquartile range (IQR)]. Baseline demographic descriptors and outcome measures wil be compared across groups by using analysis of variance for continuous variables and the $\chi$*^2^* (or Fisher exact) test for categorical variables. Within the scope of this investigation, the Generalized Estimating Equations (GEE) framework was employed to evaluate the impact of Baduanjin exercise on sarcopenia among the elderly cohort. GEE is a robust statistical approach designed to analyze correlated data or repeated measurements over time, rendering it particularly adept at accommodating incomplete datasets and multiple observational instances.Initially, an exhaustive data cleansing and encoding procedure will be undertaken to ascertain the precision and integrity of the dataset. Continuous variables will undergo a distributional analysis to discern the necessity of transformation to align with the normal distribution assumption. Categorical variables will be delineated through frequencies and percentages.The GEE model will incorporate temporal factors as a repeated measures variable, alongside other pertinent covariates that may influence the outcomes, such as age, gender, and baseline muscle mass index. The inclusion of interaction terms pertinent to time will facilitate an in-depth assessment of the longitudinal effects of Baduanjin exercise on sarcopenia. The model’s fit will be gauged using the Quasi-likelihood under the Independence model Criterion (QIC), with preference given to the model demonstrating the minimal QIC value. Additionally, a thorough examination of model residuals will be conducted to validate the adherence to underlying assumptions.Two-sided P values of less than 0.05 will be considered statistically significant. Analyses will be conducted using SPSS version 23.0 (IBM Corp) or GraphPad Prism version 7.0 (GraphPad Software).

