**3.1.4 Suspension criteria**

- Should a participant express a desire to discontinue their involvement in the study at any point, their request will be honored, and they will be withdrawn from the clinical trial.
- Participants who are untraceable or fail to attend scheduled follow-up assessments will be considered lost to follow-up and subsequently withdrawn from the study.
- In the event that a participant develops new comorbidities, complications, or undergoes physiological changes during the study that render them unsuitable for continued intervention, they will be removed from the trial.
- If a participant’s health status significantly worsens during the study, potentially leading to a critical event, and the supervising physician deems it necessary to halt the clinical trial for the individual’s safety, the participant will be withdrawn from the study.

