**3.1.5 Elimination criteria**

- Participants who are subsequently found to not fulfill the inclusion criteria after the commencement of the study will be excluded.
- Subjects who decline to participate in the prescribed examination and assessment protocol during the study will be withdrawn.
- Participants demonstrating suboptimal adherence, with cumulative exercise time falling below 80% of the prescribed amount, or those who consume medication that influences muscle or bone metabolism during the study period, will be considered non-compliant and thus removed from the trial.

1. **Sample size**

The prevalence of functional falls and fractures is a significant clinical concern and a severe consequence for patients with sarcopenia, stemming from the progressive loss of muscle mass and function. The Simple Physical Performance Measurement Scale (SPPB) serves as a pivotal efficacy indicator in this context. Drawing from extant literature ^[14]^, a 24-week exercise intervention in elderly patients with a heightened risk of falls yielded an SPPB score of 9.83 ± 1.85 in the experimental group, compared to 8.39 ± 2.52 in the control group. Employing a two-sided test with an alpha level (α) of 0.05 and a power (test efficacy) of 0.9, the calculated sample size for a single group is n = 35.6, which approximates to 36 participants. Consequently, the combined sample size for both groups amounts to 72 individuals. Factoring in a dropout rate of 20%, the total sample size required for this study is 90 cases, equating to 45 participants per group.

1. **Participant**

The proposed study aims to enroll 90 elderly patients with sarcopenia who visited the Hospital of Chengdu University of Traditional Chinese Medicine between July 2022 to August 2023. The process for inclusion involves a meticulous screening of candidates at the outpatient clinic. Potential participants are to be thoroughly informed about the study’s objectives, procedures, and potential risks. Following this educational dialogue, those who meet the study criteria and express a willingness to participate will be asked to provide informed consent and sign the corresponding consent form.

1. **Randomization and Blinding**

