The random allocation sequence was delegated to a specialized statistical analyst, who utilized the SAS 9.4 software (SAS, USA) to generate a series of random numbers ranging from 1 to 90. Subsequently, the analyst enumerated the eligible participants in sequential order of their enrollment and allocated them randomly in a balanced 1:1 ratio to either the Baduanjin exercise intervention cohort—hereinafter referred to as the ‘Baduanjin group’—or the resistance training comparator arm—hereafter denoted as the ‘control group’. The integrity of the randomization sequence was preserved by the study administrator, who remained uninvolved in participant recruitment, outcome evaluation, and statistical analysis. Upon completion of all initial assessments, participants were apprised of their group assignment via telephone.

Due to the nature of the intervention, it was impracticable to blind the study participants. Consequently, blinding was confined to the outcome assessment, data management, and statistical analysis phases. In lieu of explicit group identifiers, the designations ‘A’ and ‘B’ were employed on the case report forms to maintain anonymity. An independent statistical expert, external to the participant cohort, employed SAS software to create the blind base—a table of random numbers—which was subsequently safeguarded by the study administrator. The statistician tasked with data analysis remained uninformed about the specific intervention programs administered to each group. This blinding was only disclosed subsequent to the completion of all statistical analyses.

1. **Interventions**

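### The plan relies on unweighted GEE for incomplete data but states no missing-data assumption and fixes no working correlation, so the week-24 SPPB difference can be biased if dropout acts differently in the two arms

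*Combined protocol and SAP*

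**What the plan says.** Section 10.2 (Data analyses) makes GEE the model for the effect of Baduanjin, with time, time interactions, and covariates of which age, gender and baseline muscle mass index are given as examples. Its only remark on missing data describes GEE as "rendering it particularly adept at accommodating incomplete datasets and multiple observational instances". It prefers the model with the smallest QIC. It does not list the candidate models or say whether the rule governs covariates, interactions or the working correlation. No working correlation is named. The document states no missing-data assumption, weighting, imputation or missing-data sensitivity analysis.

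The Sample size section says "Factoring in a dropout rate of 20%, the total sample size required for this study is 90 cases", and section 10.1 repeats it: "Accounting for an anticipated dropout rate of 20%, each group necessitates 45 participants diagnosed with sarcopenia".

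Section 3.1.4 withdraws participants who miss follow-up, who develop new comorbidities or complications that make them unsuitable to continue, or on a physician's judgement "If a participant’s health status significantly worsens during the study". Section 3.1.5 removes those who complete less than 80% of the prescribed exercise time. Table 2 schedules physical function at weeks 0, 12 and 24. The Randomization and Blinding section says participants could not be blinded.

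**The concern.** GEE accepts participants with incomplete records, but that does not make its estimates valid for them. The general guarantee for unweighted GEE needs missingness that is completely at random or that depends only on covariates in the model. Worsening health, complications and poor adherence could all track physical function, which SPPB measures. Week-24 dropout could therefore depend on week-12 SPPB, which is an outcome in the model and not a covariate.

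In that situation the working correlation matters. A near-correct one uses a person's week-12 value to make up for the missing week-24 value. Independence ignores it and compares whoever is left. At stake are the week-24 difference in the primary outcome and its 5% error rate.

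**Working it through.** **1. The plan's dropout figure.** 36 / (1 − 0.20) = 45 per arm and 72 / 0.80 = 90 in total, as stated. Expected loss is 0.20 × 45 = 9 per arm. (The 36 itself does not follow from both quoted SDs: pooled SD √[(1.85² + 2.52²)/2] = 2.21 gives 2 × 2.21² × (1.960 + 1.282)² / 1.44² ≈ 49.5. That is a separate matter. Here the planned difference, 9.83 − 8.39 = 1.44, serves only as a yardstick.)

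**2. Inputs.** From the document: 45 per arm, three visits, 20% dropout. SD 2.2 is rounded from the pooled value above. Assumed, because the document is silent: visit correlations of 0.5–0.7, the dropout mechanisms below, and no true effect.

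**3. Bias under independence, by hand.** With separate means for each arm and visit, independence GEE estimates the week-24 mean from those still present. Let z be standardised week-12 SPPB and ρ the week 12–24 correlation. Then

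bias in one arm = ρ × SD × E(z | still present).

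Take a dropout probability of 1 / (1 + exp(1.6 + z)), so that low scorers leave more often. Averaged over a standard normal z, 20.7% drop out, with mean z of −0.685. Those remaining have mean z = 0.207 × 0.685 / 0.793 = 0.179. With ρ = 0.6, bias = 0.6 × 2.2 × 0.179 = 0.24 (0.20 at ρ = 0.5, 0.28 at ρ = 0.7). For the difference between arms:

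- mechanism in one arm only: 0.24;
- same mechanism in both arms, no true effect: 0.24 − 0.24 = 0;
- opposite directions: 0.24 + 0.24 ≈ 0.47.

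**4. Simulation.** Bias in the group × week-24 coefficient, 45 per arm, ρ = 0.6, true correlation exchangeable or AR(1), 300–400 trials per scenario, Monte Carlo SE 0.02–0.03. The first row was run for exchangeable truth only.

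| Dropout before week 24 | Independence | Exchangeable | Unstructured | Lowest QIC |
|---|---|---|---|---|
| Completely at random | −0.01 | 0.00 | 0.00 | 0.00 |
| On week-12 SPPB, same in both arms | −0.01 to 0.03 | 0.00 to 0.02 | −0.01 to 0.02 | −0.01 to 0.03 |
| On week-12 SPPB, one arm only | 0.24 to 0.27 | 0.00 to 0.05 | 0.00 to 0.03 | 0.19 to 0.23 |
| Opposite directions | 0.50 to 0.51 | 0.04 to 0.08 | 0.05 to 0.06 | 0.47 to 0.49 |

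Two further sets used correlations of 0.5–0.7. One (1,500 trials per scenario) gave absolute bias of 0.24 (one arm) and 0.54 (opposite) under independence, 0.01 and 0.09 under exchangeable, and 0.00–0.03 with likelihood-type estimation. The other gave 0.40–0.69 under independence for arm-dependent dropout, 0.09–0.12 under exchangeable, and 0.04 or less with likelihood-type estimation.

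**5. Error rate.** With 36 per arm at week 24, SE ≈ 2.2 × √(2/36) = 0.52. A bias of 0.24 is 0.46 SE, so the two-sided 5% test rejects with probability Φ(−1.50) + Φ(−2.42) ≈ 7.5%. A bias of 0.54 is 1.04 SE, giving Φ(−0.92) + Φ(−3.00) ≈ 18%. The simulated rates under independence were 7.3% and 18%.

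**6. Against the planned effect.** 0.24 / 1.44 = 17%; 0.51 / 1.44 = 35%; 0.69 / 1.44 = 48%.

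**7. QIC.** With a common scale parameter across fits, QIC preferred independence in 64–91%, 68–90% and 87–99% of runs in the three sets. In a smaller check of one-arm dropout (120 trials), the share was 87.5% with a common scale and 5% when each fit used its own estimated scale. SPSS's own QIC was not reproduced.

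**The case against.** A reader might infer that GEE is valid only when data are missing completely at random. That is too strong. Missingness that depends only on modelled covariates is also covered, and the exchangeable and unstructured fits above were nearly unbiased when dropout depended on week-12 SPPB.

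A reader might also infer that choosing by lowest QIC makes the bias worse. The plan does not say that QIC selects the working correlation; the sentence follows a description of covariates and time interactions. In the arm-dependent scenarios the lowest-QIC model was slightly less biased than independence (0.19 against 0.24; 0.49 against 0.51). It was worse only than a fixed, suitable correlation. How often QIC picks independence depends on the scale convention, so no percentage above describes this plan in SPSS.

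The withdrawal rules apply identically to both arms, and the document gives no reason for dropout to run in opposite directions. When the mechanism is shared and there is no true effect, every version of GEE is about unbiased. The larger figures come from assumed arm-differential dropout. Some dropout, such as sudden deterioration, may not be predictable from week-12 SPPB, and then a mixed model does not cure it either.

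All of this stands and limits the size of the point. It does not supply what the plan lacks: a stated assumption, a fixed correlation structure and a sensitivity analysis. Unblinded participants doing different exercise make some arm-differential dropout plausible, though not established.

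**Conclusion.** The point holds as a specification gap that can bias the primary result, and it should be closed before the data are analysed. Section 10.2 treats GEE as sufficient for incomplete data without saying under what assumption, and leaves open the feature that decides how much harm dropout does.

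The size depends on a mechanism the document does not give. The range runs from about zero (shared mechanism, no true effect), through roughly 0.2–0.4 SPPB points (one arm only, independence), to 0.5–0.7 (opposite directions, independence, an extreme case). A suitable correlation or likelihood-type estimation brings this to about 0.0–0.1. All figures rest on SD 2.2, visit correlations of 0.5–0.7 and about 20% missing at week 24. The documents do not support saying that GEE is invalid here, or that the QIC rule by itself creates the bias.

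**What to change.** - **Primary analysis.** Prespecify a REML mixed model for repeated measures with group, visit, group × visit and the chosen covariates, and unstructured covariance across weeks 0, 12 and 24 (SPSS MIXED). It is valid under missing at random. Alternatively, keep GEE with a fixed unstructured working correlation after multiple imputation by arm using earlier SPPB.
- **QIC.** Do not use it to choose the working correlation. If it keeps any role, say which terms it may select and list the candidates.
- **Wording.** Replace the sentence crediting GEE with handling incomplete data by the missing-data assumption actually made.
- **Sensitivity.** Add one delta-adjusted analysis for data missing not at random. With 20% missing, shifting imputed week-24 values in one arm by δ moves the difference by 0.2δ, so δ = 1.44 moves it by 0.29. A reference-based analysis suits this trial poorly because both arms are active exercise.

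Cost: SAP wording and a little more analysis, the mixed model being available in SPSS, which the plan already names. Sample size, visits and procedures do not change. The mixed model relies on approximate normality of a score bounded at 0 and 12, so the residual checks already planned should be kept.

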**7.1 The Baduanjin Group**

In conjunction with health education initiatives, the Baduanjin training is conducted at a designated time and location. Each session is facilitated by an instructor with a minimum of five years’ experience in teaching Baduanjin. The training adheres to the Baduanjin standards promulgated by the State General Administration of Sports in 2006 ^[15]^. The sequence comprises a preparatory stance followed by a series of ten movements:

- Preparatory Posture
- Holding Up The Sky With Both Hands To Regulate The Sanjiao
- Draw The Bow On Both Sides As If To Shoot A Vulture
- Stretch Arms Asymmetrically To Enhance Spleen And Stomach Function
- Look Back To Treat Five Strains And Seven Impairments
- Sway The Head And Buttocks To Subdue The Heat Fire
- Touch Feet To Strngthen Kidneys And Waist
- Rise Up On Toes And Land On Heels Repeatedly To Cure Disease
- Clench The Fist And Open Eyes Wide To Enhance Vitality
- Closing Posture

The regimen is scheduled three times weekly, with each session lasting 60 minutes. This includes 15 minutes for warm-up activities, 30 minutes dedicated to the Ba Duan Jin exercises, and 15 minutes for cool-down activities, spanning a total duration of 24 weeks.

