**7.2 The Resistance training Group**

The educational component of the study on sarcopenia in the elderly is structured to provide sessions once every four weeks, each lasting no less than 30 minutes. These sessions are designed to impart knowledge on the risk factors, adverse consequences, and preventive measures associated with sarcopenia. An example of such preventive measures includes adherence to the dietary guidelines for the elderly, as revised in 2016 by the Chinese Nutrition Society, which emphasizes rational nutrition, balanced diets, and the cultivation of healthy living and eating habits. In terms of physical intervention, the study incorporates a resistance training program tailored to the geographic location of each sub-centre. The regimen consists of 60-minute sessions conducted three times a week over a 24-week period. Each training session is segmented into a 15-minute warm-up, followed by 30 minutes of resistance exercises—including Wall squat, Wall push-up, Forward lunge, Reverse triceps push-up, and Wall-supported calf raise—and concludes with 15 minutes of cool-down activities.

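### Participants are trained in coach-led classes, but the GEE in 10.2 allows only for repeated visits; if class effects differ by arm, the SPPB standard error is too small

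*Combined protocol and SAP*

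**What the plan says.** Section 6 allocates individual participants 1:1. Delivery is then in groups. In section 7.1, "the Baduanjin training is conducted at a designated time and location. Each session is facilitated by an instructor". Section 7.2 describes "a resistance training program tailored to the geographic location of each sub-centre" and names no instructor. Section 9.3 is not limited to one arm: it has certified coaches instructing throughout, requires that "participants unable to attend centralized sessions were required to request and log their absence in advance", and says that "indoor facilities like community centers were strategically selected as the venues for the intervention". Section 8.3 starts fall recording at the first intervention class.

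For the analysis, section 10.2 states: "The GEE model will incorporate temporal factors as a repeated measures variable, alongside other pertinent covariates that may influence the outcomes". The covariates it gives as examples are age, gender and baseline muscle mass index. No class, instructor, venue or sub-centre appears there as a model term or clustering unit. Section 10.1 sizes the trial without a design effect: "the requisite sample size for a single intervention group is deduced to be approximately 36".

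**The concern.** People who train together three times a week share a coach, a room and each other's company, so their follow-up SPPB scores may be more alike than those of people in different classes. The two arms do different exercises, so a class would hold members of one arm only. Class effects then add to the variance of the arm difference instead of cancelling from it.

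The robust variance of a GEE protects against misspecified correlation within its clusters, but it assumes independence between them. Here the clusters are participants, so correlation between classmates is left out.

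At stake is the meaning of the primary result: one strong or weak class or coach could be reported as an effect of exercise type. The same applies to grip strength, walking speed, body composition and MoCA if they use the same model.

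**Working it through.** **Inputs from the documents.** Test level: "Two-sided P values of less than 0.05 will be considered statistically significant" (10.2). Design: "an alpha level (α) of 0.05 and a power (test efficacy) of 0.9" (section 4, Sample size). SPPB 9.83 ± 1.85 against 8.39 ± 2.52, a difference of 1.44; 36 per group before dropout and 45 after (section 4). SPPB is measured at weeks 0, 12 and 24 (Table 2).

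**Assumptions, not in the documents.** Equal class sizes *m*; ICC 0.05, range 0.01 to 0.10; each class in one arm; 36 analysed per arm.

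**Step 1: the plan's own figure.** The formula is n = 2 × [SD × (1.960 + 1.282) / 1.44]².
- With SD 1.85 in both arms, n = 34.7. Adding the small-sample term 1.96²/4 = 0.96 gives 35.65, in line with the stated 35.6.
- With both quoted SDs, root mean square √[(1.85² + 2.52²)/2] = 2.21, n = 49.5.
- The dropout step reproduces: 36/0.8 = 45.

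The choice of SD is a separate matter. For this point, what counts is that neither calculation has a term for classes.

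**Step 2: effect on the 5% level.** With classes of size *m* nested in arm, the variance of an arm mean is multiplied by DE = 1 + (m − 1) × ICC. A test that ignores this rejects a true null with probability 2 × [1 − Φ(1.96/√DE)]. For m = 9 and ICC 0.05, DE = 1 + 8 × 0.05 = 1.40, 1.96/√1.40 = 1.66, and the rate is 9.8%.

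| Classes per arm × size | DE at ICC 0.05 | Rate, ICC 0.01 | Rate, ICC 0.05 | Rate, ICC 0.10 |
|---|---|---|---|---|
| 9 × 4 | 1.15 | 5.3% | 6.8% | 8.6% |
| 4 × 9 | 1.40 | 5.9% | 9.8% | 14.4% |
| 3 × 12 | 1.55 | 6.3% | 11.5% | 17.6% |
| 2 × 18 | 1.85 | 7.0% | 15.0% | 23.3% |
| 1 × 36 | 2.75 | 9.2% | 23.7% | 35.6% |

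Simulation of a participant-level t-test (40,000 trials per setting, SDs 1.85 and 2.52) agrees. At ICC 0.05 it gave 9.8%, 11.4%, 15.1% and 24.8% for four, three, two and one classes per arm, and 5.0–5.1% at ICC 0. At ICC 0.10 it ran from 14.9% to 37.0%.

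A three-visit GEE clustered on participant was also simulated (45 per arm, ICC 0.05 on follow-up visits, assumed within-person correlation 0.6, 600 runs per setting). It gave about 10%, 12%, 14%, 16% and 30% for classes of 5, 10, 15, 22 and 45, against 5.3% at ICC 0. With 600 runs these are rough: the Monte Carlo standard error near 12% is √(0.12 × 0.88/600) = 1.3 percentage points.

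**Step 3: effects shared by both arms.** If half of the class variance is common to both arms, the t-test rates at ICC 0.05 fall to about 6.9%, 7.9%, 9.8% and 15.7% for four, three, two and one classes per arm. If all of it is common, there is no inflation (about 4.5–5.0%).

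**Step 4: effect on power.** At ICC 0.05, with the plan's difference and both SDs, a test on class means holds 5% and has power of about 51% (four classes per arm) or 41% (three). The participant-level test appears to have 74%. Without clustering, 36 per arm gives about 79%.

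**The case against.** A reader might infer that the SPPB test has a true false-positive rate of 10–25%. The documents do not support that. At ICC 0.05 this range needs classes of about 9 to 39, and neither class size nor ICC is given. Small classes or a small ICC leave the rate at about 5–9%.

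Other points also stand:
- The plan does not say that participants are independent; this is inferred from what the model leaves out. The covariate list is by example only, so a class term is not ruled out. But a covariate that might be added later is not a pre-specified clustering level.
- The documents do not say whether the arms share venues or coaches. Whatever is shared cancels.
- A coach in the resistance arm is inferred from section 9.3, since 7.2 names none. That section's call for uniform, standardised movements should also limit differences between coaches.

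These points limit the size of the problem. They do not remove it, because peer effects and arm-specific instruction remain possible and nothing in 10.2 would detect or absorb them.

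**Conclusion.** The point holds in conditional form. The documents show individual randomisation, group delivery and an analysis with no level for class. If class effects are nested in arm, the standard error of the SPPB contrast is too small.

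With 36 analysed per arm and ICC 0.05, the illustrative false-positive rate is about 7% with classes of 4 or 5, 10% with four of 9, 11–12% with three of 12, 15% with two of 18 and 24% with one of 36. From four classes down to one per arm it is about 6–9% at ICC 0.01 and 15–37% at ICC 0.10. All of these fall if part of the class effect is common to both arms. They rest on an assumed ICC, assumed equal class sizes and one arm per class, so they show what could happen and do not estimate this trial's error rate.

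**What to change.** 1. **Record** class, instructor and venue for each participant beside the attendance data already kept under 7.5 and 9.3, and state the number of classes and instructors per arm.

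2. **Model, in 10.2.** Analyse SPPB at weeks 12 and 24 with baseline SPPB as a covariate; arm, visit and arm-by-visit as fixed effects; random intercepts for class nested in arm and for participant; and Satterthwaite degrees of freedom (available in SPSS MIXED). In a simulated single-visit equivalent at ICC 0.05, the false-positive rate was 4.4% with four classes per arm, 4.5% with three and 6.5% with two, so two classes per arm remain mildly liberal.

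3. **Avoid a correction that does nothing.** If week 0 stays in the model as an outcome visit, use a random class-by-visit (post-baseline) term. A class intercept that is constant over all visits enters week 24 and week 0 equally and drops out of their difference. In a fitted example the arm-by-visit standard error was 0.484 with or without such an intercept, against 0.536 with a class-by-visit term.

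4. **One class or one instructor in an arm.** Class and arm then cannot be separated. Report the interval also widened by √[1 + (m − 1) × ICC] for ICC 0.01, 0.05 and 0.10 (for m = 36, factors of √1.35 = 1.16, √2.75 = 1.66 and √4.5 = 2.12), and limit the conclusion to the classes studied.

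5. **Sections 4 and 10.1.** State that the power figure assumes no class clustering.

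The cost is one set of identifiers and SAP wording, with no added patients. The price is a wider interval, fewer degrees of freedom and lower real power than the plan states.
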